## Abstract

**Background:**

Twin-to-twin transfusion syndrome (TTTS) is a serious complication of 10–15% of twin or triplet pregnancies in which multiple fetuses share a single placenta. Communicating placental vessels allow one fetus (the donor) to pump blood to the other (the recipient). Mortality rates without intervention are high, approaching 100% in some series, with fetal deaths usually due to cardiac failure. Surgical correction using laser photocoagulation of communicating placental vessels was developed in the 1980s and refined in the 1990s. Since it was introduced in Victoria in 2006, laser surgery has been performed in approximately 120 pregnancies.

Survival of one or more fetuses following laser surgery is currently > 90%, however the neurodevelopmental outcomes for survivors remain incompletely understood. Prior to laser therapy, at least one in five survivors of TTTS had serious adverse neurodevelopmental outcomes (usually cerebral palsy). Current estimates of neurological impairment among survivors following laser surgery vary from 4 to 31% and long-term follow-up data are limited.

**Methods:**

This paper describes the methodology for a retrospective cohort study in which children aged 24 months and over (corrected for prematurity), who were treated with laser placental photocoagulation for TTTS at Monash Health in Victoria, Australia, will undergo comprehensive neurodevelopmental assessment by a multidisciplinary team. Evaluation will include parental completion of pre-assessment questionnaires of social and behavioural development, a standardised medical assessment by a developmental paediatrician or paediatric neurologist, and age-appropriate cognitive and academic, speech and fine and gross motor assessments by psychologists, speech and occupational therapists or physiotherapists. Assessments will be undertaken at the Murdoch Children’s Research Institute/Royal Children’s Hospital, at Monash Health or at another mutually agreed location. Results will be recorded in a secure online database which will facilitate future related research.

**Discussion:**

This will be the first study to report and evaluate neurodevelopmental outcomes following laser surgery for twin-to-twin transfusion syndrome in Victoria, and will inform clinical practice regarding follow-up of children at risk of adverse outcomes.

**Electronic supplementary material:**

The online version of this article (10.1186/s12887-018-1230-8) contains supplementary material, which is available to authorized users.

## Background

### Multiple pregnancy and types of twinning

When a single fertilised egg (zygote) splits into two embryos, a monozygotic twin pregnancy results. This occurs spontaneously in 1 in 250 pregnancies [1]. When a single embryo splits, in ¾ of cases, the developing genetically identical fetuses share a single placenta and are described as “monochorionic”. For monozygotic twins (and more rarely, triplets) who share a placenta, there are significant associated risks, with a 3 and 7-fold increased risk of perinatal illness and death respectively, compared with singletons [2]. They are 9 times more likely to die in utero than identical twins who do not share a placenta, with a perinatal mortality rate of 12% when born at or after 32 weeks [3]. Premature birth is a significant risk for monozygotic multiples, with 63% of twins and all triplets born prior to 37 weeks [4, 5].

### Pathophysiology of twin-to-twin transfusion syndrome

In 10–15% of monozygotic monochorionic pregnancies, blood flows unequally along placental blood vessels known as anastomoses [6]. This condition is known as “twin-to-twin transfusion syndrome” (TTTS). One fetus (identified as the donor) “pumps” blood to the other (the recipient). This situation is extremely hazardous for both.

The donor twin may become severely anaemic; urine output diminishes, growth falters and their amniotic sac empties and shrinks (oligohydramnios). Such a fetus may ultimately become adhered to the membranes (“stuck twin”). Should it survive to birth, his or her lungs may not have developed adequately. At birth, a donor may appear small, malnourished and pale. In contrast, the recipient is at risk of blood volume overload. This fetus attempts to compensate by increasing urine output. Excessive urine production then distends their amniotic sac (polyhydramnios). At birth the recipient may appear large, swollen and red. Accumulation of amniotic fluid may cause uterine contractions, with pressure on the uterus and cervix triggering premature labour or precipitating preterm premature rupture of the membranes.

TTTS usually becomes clinically evident during the mid-trimester (16–21 weeks). Signs may include a rapid and marked increase in a mother’s abdominal girth, due to the recipient’s expanded amniotic fluid compartment. However, subclinical TTTS is often identified on ultrasound earlier in the pregnancy. The onset may be slow (over weeks) or acute and catastrophic. The diagnosis of TTTS is based on strict ultrasonographic criteria [7], of which the most widely used is the Quintero staging system [8]. The possibility of TTTS is one of the reasons behind frequent antenatal ultrasound monitoring of monochorionic pregnancies.

### Natural history

Mortality from severe untreated TTTS is extremely high, with rates between 70 and 100% reported [9, 10]. Deaths occurring in utero are usually attributable to fetal cardiac failure. Without treatment, pre-viable or extremely preterm births contribute to high perinatal mortality. Of twins that are liveborn, a significant proportion suffer from postnatal complications of TTTS, including heart and kidney dysfunction and complications of polycythaemia and anaemia [10, 11].

### Selective Fetoscopic laser photocoagulation of placental anastomoses (SFLP or “laser surgery”)

In 1983, [name] De Lia and colleagues began developing a novel therapy for TTTS. Working initially with sheep (which have a naturally high rate of identical twinning), and subsequently humans, they pioneered the procedure of fetoscopic placental laser surgery [12]. Quintero and colleagues subsequently demonstrated superiority of a selective over a non-selective approach to obliteration of vessels at the vascular equator [13]. In a further refinement, points of coagulation were joined by a line of coagulation across the vascular equator (Solomon technique). This technique significantly reduced post-laser complications of recurrent TTTS and twin anaemia polycythaemia sequence (TAPS, an atypical chronic form of TTTS) [14].

Prior to the development of laser surgery, the only management options for TTTS were palliative, including amnioreduction (drainage of excess amniotic fluid to relieve uterine pressure) or septostomy (creating a hole in the inter-fetal membrane allowing equalisation of fluid). In cases of fetal malformation, selective termination of one fetus was employed in the hope of improving outcomes for the less affected fetus/es.

Unlike amnioreduction and septostomy, SFLP offers a cure for the underlying pathological process. The procedure identifies and physically disrupts the anastomosing vessels, thereby preventing transfusion of blood from donor to recipient [15]. Initially performed using an open approach with laparotomy, SFLP now usually uses a minimally invasive laparoscopic technique. Maternal physical recovery from the procedure is prompt. Rarely, a second (repeat) laser procedure is required should TTTS recur or post-laser TAPS develop, either as a result of a “missed” vessel/s, or as a novel episode [16]. Surgical failure may occur in up to 18% of procedures [7] and preterm labour and preterm premature rupture of membranes also contribute to post-operative perinatal morbidity and mortality.

In 2004, a randomised controlled trial comparing laser surgery with (then-standard) serial amnioreductions had to be discontinued early when interim analysis demonstrated clear superiority of laser in terms of survival and survival without major disability [17]. SFLP is now first line treatment for all but the mildest cases of TTTS, and a randomized controlled trial is currently underway, examining the role of SFLP in Stage 1 TTTS [18].

### Australian experience with laser surgery, and the Victorian fetal therapy service (VFTS)

The first fetal laser surgery for TTTS in Australia was performed at the Mater Hospital in Brisbane in 2002 [19]. Today, SFLP is offered in four Australian states: Queensland, New South Wales, Western Australia and Victoria. The Victorian Fetal Therapy Service (VFTS) is a three-centre collaboration between Monash Health, Mercy Hospital for Women (MHW) and The Royal Women’s Hospital (RWH), with surgery conducted at Monash Health. Reported outcomes have been consistent with international experience [14, 17, 20, 21], with 68% overall infant survival, and survival of one or more twin/s in 86% of gestations treated.

Regrettably, in Melbourne to date there has been no formal system for routine neurodevelopmental follow-up of surviving children. Although at elevated risk of neurodevelopmental disability, follow-up has been at the discretion of the clinicians involved in the children’s postnatal care. Lack of consistency of follow-up may have resulted in missed opportunities for early detection of developmental difficulties, and valuable information has not been collected.

### Neurodevelopmental outcomes following TTTS

Prevalence of severe neurodevelopmental abnormalities among monochorionic twins who *did not* suffer from TTTS is between 4 and 8% [22]. Survivors of TTTS have been demonstrated to be at further increased risk of adverse neurodevelopmental outcomes. Prior to widespread adoption of SFLP, rates of neurological disability documented among TTTS survivors ranged between 17% [23] and 42% [24].

Van Klink and colleagues [25] summarised 13 studies from 1999 to 2016, reporting neurodevelopmental outcomes following laser surgery. Observed rates of cerebral palsy ranged between 3 and 12%, and rates of neurodevelopmental impairment (cerebral palsy, severe cognitive and/or motor delay (< 2 SD), blindness and/or deafness) were 4–18%. Table 1 summarises an additional 4 studies. Lower prevalence of disability has been identified following briefer periods of follow-up (6 months-2 years) and using less structured review procedures, and higher prevalence with longer duration of follow-up and more rigorous evaluation.

**Table 1 Tab1:** Developmental Outcomes following laser for TTTS (subset of published studies)

Author and year	Number and age of participants	Measures	Outcomes
Campos, D., et al., (2016) [35]	*N* = 33 monochorionic diamniotic twins (post-laser), and *N* = 22 term singletons Birth to 12 months, corrected for prematurity	Bayley Scales of Infant Development, Clinical examination of TTTS group. Two assessments, in first and second 6 months of life.	Cerebral palsy in 18%, strabismus in 9%, microcephaly in 3% of TTTS group. Significant difference between groups in prevalence of cognitive and fine motor deficits apparent by 6 months (greater risk in TTTS group); by 12 months, significantly greater prevalence of deficits in all domains for TTTS group Comparative results at second assessment not provided (table of first assessment repeated in error). Donors 7 times increased risk of adverse outcomes c.f. recipients; donor status and low socioeconomic status, and cardiorespiratory disease were associated with poorer expressive communication & fine motor skills respectively
Müllers, S. et al., (2015) [36]	*N* = 106 (post-laser). Median age 4 years (range 6 mo – 7 yrs) (correction for prematurity not specified)	Individual correspondence and paediatric evaluation (details not specified)	Ongoing neurodevelopmental concerns in 14% (speech and language concerns *n* = 7, behavioural concerns *n* = 2, mild motor delay n = 2, mild cerebral palsy n = 2, major cerebral palsy n = 2)
Tosello, B. et al., (2014) [29].	*N* = 35 (post-laser). Median age 37 months, mean 30 mo (range 4 mo - 5 yrs)	Neurological assessment at discharge from maternity hospital. Ages and Stages Questionnaire (ASQ) at up to 5 years	As neonates, ≈7% neurologically abnormal (≈93% normal). At follow-up, ≈31% abnormal based on ASQ (≈69% normal), ≈6% severely neurologically abnormal (cerebral palsy). Of children found to be abnormal at follow-up, 45% had not been detected on routine medical review. Donor status and birth < 32 weeks significantly associated with adverse neurosensory outcome as neonates. No correlations at follow-up between outcome and donor status, severity of TTTS or other variables (but small numbers)
Sago, H. et al., (2010) [37]	*N* = 275 (post-laser). Age 6 months (correction for prematurity not specified)	Review of cerebral imaging & clinical assessment by paediatrician (details not specified)	Major neurological disability in ≈5% (severe IVH, cystic PVL, CP, hydrocephalus, ventriculomegaly, or multiple infarcts)

Characterisations of neurodevelopmental outcomes in the literature have been problematic and managed inconsistently, for several reasons. First, developmental status is often reported as a categorical variable (“impaired” vs “unimpaired”), whereas a more conceptually sound framework sees neurodevelopment on a continuum of ability [26]. Further, neurodevelopment is not a single entity, but is conceptualised as comprising a number of domains, any one of which may be impaired either in isolation or in combination. Assigning a child to an “outcome” implies that this outcome is fixed, and ignores that change is fundamental to the construct of neurodevelopment.

Thus far, reports of measures of social or emotional development, or academic achievement, have been lacking. Findings regarding language have relied on subscales of global measures of intelligence, rather than specific measures of speech and language. This is a considerable oversight, given the documented high prevalence of language disorders among children of multiple birth [27, 28]. Consideration of lesser degrees of neurodevelopmental impairment has also been overlooked. Severe outcomes such as cerebral palsy have been reported, but prevalence estimates of relatively minor morbidities (such as specific learning impairments) that may nonetheless have significant impacts on the lives of survivors and their families are not available. The most common approach in reporting of outcomes has been a three-tier categorisation of “Normal”, “Mild impairment”, and “Severe impairment”. Children involved in this study will be similarly grouped allowing comparison with previous reports, but due to the limitations of this approach, alternative outcomes, described in the methods, will also be reported.

### Study aims

The study will assess child survivors of TTTS-affected multiple pregnancies managed by fetal laser surgery in Victoria for the presence of neurodevelopmental disabilities, and will establish a database of obstetric, neonatal and paediatric data relating to this disorder. The database will serve as a model for future, prospective research involving children at risk of developmental disabilities.

## Method

Approval for the study was obtained from the Human Research Ethics Committees (HRECs) of the Royal Children’s Hospital (reference 34269D) Royal Children’s Hospital (reference 34269D), Monash Health (reference RES-17-0000-149X), Mercy Hospital for Women (reference R15/24) and The Royal Women’s Hospital (reference HREC/15/RCHM/37). Consent is informed opt-in by parent or legal guardian (either written or verbal, which in the latter case must be documented by a researcher). A separate consent form will be completed for each participating child. Consent forms will be kept in a locked cabinet on MCRI premises, and scanned into the database.

### Study design

The proposed study is a retrospective cohort study assessing neurodevelopmental outcomes for survivors of TTTS managed with laser photocoagulation in Melbourne, Australia, from 2006 to 2015 inclusive.

### Study setting

The study will be coordinated through the department of Developmental Disability and Rehabilitation Research, at the Murdoch Children’s Research Institute (MCRI). Monash Health was the location of all laser surgery. Follow-up assessments will be conducted at either of the two tertiary children’s hospitals in the Australian state of Victoria, or in the family home (depending on family preference), with reimbursement of travel expenses and hospital parking fees. The relevant departments at The Royal Children’s Hospital and Monash Health are Neurodevelopment and Disability and Monash Paediatric Rehabilitation Service, respectively. The research team will consist of a doctor, psychologist, speech therapist, physiotherapist or occupational therapist and a study coordinator. For each participating family, appointments will be scheduled to take place on a single day.

### Participants

The study includes surviving twin (or triplet) child participants, aged 24 months or more (corrected for prematurity), and their parents or carers who will report on the abilities and behaviour of their child/ren. Where survival is not documented or is not known, the family will be approached in a sensitive manner to ascertain eligibility.

#### Number of participants

Approximately 100 procedures have been undertaken within the specified range. Overall survival has been reported at 68% [20]. Assuming twin gestations, approximately 136 children are eligible for the study (100 × 2 × 0.68).

### Procedure: Recruitment strategy

Recruitment strategy is outlined in Fig. 1 below.

**Fig. 1 Fig1:**
[figure not shown]
Recruitment strategy

#### Loss to follow-up

Previous similar studies have identified a loss to follow up proportion of up to 20% at a median age of 37 months [29]. As the present study involves a greater time since the procedure (up to 11 years, in the case of procedures performed in 2006), the proportion lost to follow up is likely to be higher.

As far as possible, characteristics of potential participants lost to follow-up will be compared with those able to be followed up, to identify whether significant differences (in terms of characteristics such as severity of TTTS) exist between groups. Previous studies have not found significant differences between these groups.

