## Discussion: Ethical considerations

### Sensitivity to bereavement

As a high-risk population, it is anticipated that a significant proportion of parents will be bereaved of one or more children. It is for this reason that birth and postnatal records will be reviewed prior to recruitment. Although no parent who lost both twins or all triplets will knowingly be invited to participate, it is theoretically possible that a parent may receive written study information before the researchers become aware of the bereavement. For this reason, the Introductory Letter from the laser clinician is non-specific. The Participant Information Statement includes the following text:

“Please note: We have tried very hard to avoid sending project information to parents whose children have both / all passed away. If you are in this situation and you have received this by mistake, please accept our sincerest apologies and condolences, and kindly disregard the information.”

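### The check on children lost to follow-up relies on finding significant differences, a criterion that would often miss a sizeable imbalance in a cohort this small

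*Protocol article*

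**What the plan says.** Under Loss to follow-up, the protocol article cites earlier work with a "loss to follow up proportion of up to 20% at a median age of 37 months" and expects a higher proportion here, because up to 11 years will have passed since surgery. It then states its check. As far as possible, the characteristics of lost and followed children will be compared "to identify whether significant differences (in terms of characteristics such as severity of TTTS) exist between groups". The section closes with "Previous studies have not found significant differences between these groups".

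The Data analysis section says that p values will serve to judge how strong an association is, and that results will be given as percentages of participants. It sets no significance level. It describes no weighting, bounds or other allowance for children who are not assessed, and rules none out.

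On the data available for non-participants, the Sensitivity to bereavement section says that "birth and postnatal records will be reviewed prior to recruitment". The optional component under Measures makes requests for information from the birth hospital subject to parental consent, and lists TTTS severity among the facts that parents may not know.

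**The concern.** The share of survivors with impairment is the study's main product. The Implications section links it to whether all survivors should be followed up routinely. Consent is opt-in, and participation brings a free multidisciplinary assessment with possible referral. Attendance could therefore depend on how worried a family is, in either direction.

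Two things limit the stated check. First, significance depends on sample size as well as on the size of the imbalance. With a small lost group, a substantial difference can easily be non-significant, so failing to find one says little about representativeness. Second, the comparison uses background characteristics. Two groups can match on stage and still differ in the rate of impairment. The closing remark about earlier studies has the first weakness too. The study cited for the 20% figure had 35 children, and Table 1 itself warns of small numbers when reporting that study's null results at follow-up.

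**Working it through.** **Inputs from the protocol article**
- Procedures: "Approximately 100 procedures have been undertaken within the specified range" (Number of participants).
- Infant survival: 68% (same section).
- Pregnancies with a survivor: "survival of one or more twin/s in 86% of gestations treated" (Australian experience section).
- Loss: above 20%, with no figure given.

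**Assumptions, not in the document**
- One procedure per twin pregnancy, and both survival figures apply to the study window.
- Loss of 20% to 50%.
- Two-sided significance level 0.05.
- Severe stage in 50% of followed and 70% of lost; 50% v 65% as a smaller imbalance.
- Families are followed or lost as a whole.
- Observed prevalence of 10% for illustration.

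**Step 1. The plan's own figure.** 100 × 2 × 0.68 = 136 eligible children, as stated. Pregnancies with at least one survivor: 100 × 0.86 = 86.

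**Step 2. Group sizes.** At 20% loss: 109 v 27 children, or 69 v 17 pregnancies. At 40% loss: 82 v 54 children, or 52 v 34 pregnancies.

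**Step 3. Power of the comparison.** Power = Φ[(d − 1.96 × SE0) / SE1], where d is the difference in proportions, SE0 = √[p̄(1 − p̄)(1/n1 + 1/n2)] and SE1 = √[p1(1 − p1)/n1 + p2(1 − p2)/n2].

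Per pregnancy, 50% v 70%, 20% loss:
- p̄ = (69 × 0.5 + 17 × 0.7)/86 = 0.5395
- SE0 = 0.1350, SE1 = 0.1264
- Power = Φ[(0.20 − 1.96 × 0.1350)/0.1264] = Φ(−0.51) ≈ 0.30

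Per pregnancy, 50% v 70%, 40% loss:
- p̄ = (52 × 0.5 + 34 × 0.7)/86 = 0.5791
- SE0 = 0.1089, SE1 = 0.1048
- Power = Φ[(0.20 − 1.96 × 0.1089)/0.1048] = Φ(−0.13) ≈ 0.45

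All scenarios:

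| Loss | 50% v 70%, per child | 50% v 70%, per pregnancy | 50% v 65%, per child | 50% v 65%, per pregnancy |
|---|---|---|---|---|
| 20% | 46% | 30% | 28% | 19% |
| 30% | 58% | 40% | 36% | 24% |
| 40% | 64% | 45% | 41% | 27% |
| 50% | 67% | 47% | 42% | 29% |

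Stage is shared by all children of a pregnancy, so the per-pregnancy columns are the relevant ones for it. No scenario reaches 80%. From a base of 50%, the difference detectable with 80% power per pregnancy is about 35 points at 20% loss and 29 points at 50% loss.

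**Step 4. What loss can do to the prevalence.** If p is the observed prevalence, L the proportion lost and k the risk in the lost relative to the followed, the cohort prevalence is (1 − L) × p + L × k × p. With p = 10%:

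| Loss | k = 0.5 | k = 1 | k = 2 |
|---|---|---|---|
| 20% | 8% + 1% = 9% | 8% + 2% = 10% | 8% + 4% = 12% |
| 40% | 6% + 2% = 8% | 6% + 4% = 10% | 6% + 8% = 14% |

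The logical extremes (none or all of the lost impaired) are 8% to 28% at 20% loss and 6% to 46% at 40% loss. These extremes follow from any loss of that size and are no defect of this plan. They show what the baseline comparison leaves open.

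**The case against.** The strongest reply is that the plan claims less than a critic might read into it. A reader might infer that a non-significant result will be taken as proof of no selection. The document states no such rule: it sets no level and no pass mark, and its remark on earlier studies describes other work. A reader might also infer that the prevalence will never be corrected. The document does not support that either. It is a condensed article, it excludes nothing, and weighting or sensitivity tables are commonly placed in a fuller protocol or analysis plan that is not shown.

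A third tempting reading is that full records on every survivor are already to hand. The pre-recruitment review is described for one purpose, to avoid contacting bereaved parents, and birth-hospital information otherwise needs consent. The plan itself says only that the comparison will be made as far as possible. Weighting is therefore not simply available. With 17 lost pregnancies, a model with five predictors would have 17/5 = 3.4 lost pregnancies per predictor, and weights built on background variables would not remove attendance that depends on the child's outcome.

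Finally, the size of the imbalance is assumed. At 40% loss the per-child power for 50% v 70% is 64%, so it would be wrong to say that the check would usually pass in every case.

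All of this stands, and it narrows the point. It does not rescue significance as the stated yardstick. The article does fix that choice, and the sample cannot support it.

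**Conclusion.** The concern holds in a limited form. The article names a search for significant differences as its check on representativeness. For a pregnancy-level trait such as severity, that check would miss a 20-point imbalance more often than not: power is about 30% at 20% loss, 45% at 40% and 47% at 50%. This rests on 86 pregnancies, a 50% v 70% split and a two-sided level of 0.05, of which the split and the level are assumptions. The check also cannot address attendance driven by the child's outcome, which could move an observed 10% to 12% at 20% loss, or to 14% at 40% loss, if the lost had twice the risk. On correction, the most that can be said is that none is described in this article. The change is worth making, because the stated criterion is a poor one and a better one costs little.

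**What to change.** In Loss to follow-up, replace the search for significant differences with wording such as:

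*Assessed and unassessed survivors will be described side by side on the characteristics available for all survivors (for example stage and year of surgery, where records permit). Standardised differences, or differences with 95% confidence intervals that account for pregnancy, will be reported, and the groups will not be judged alike or unlike by p value. Prevalence of impairment will be reported with a table of its value if unassessed children had 0.5, 1 and 2 times the observed risk.*

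The table needs only the number of unassessed survivors, so it does not depend on consent to obtain their records. It is also the only part that speaks to outcome-dependent attendance. Inverse-probability weighting can be added as an option, restricted to the few covariates that exist for non-participants. The closing remark on earlier studies should be removed or qualified by their size.

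The cost is a little more analysis and a few sentences of text. The drawback is a headline prevalence that is shown with wider uncertainty.
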